#### Secondary outcomes

For the secondary outcome pertaining to prostatic levels of inflammation mediators, the t-tests (or Wilcoxon rank-sum test) will be used to compare levels across groups.

Blood levels of inflammation biomarkers as well as outcomes concerning quality of life are measured at multiple time points. For these analyses, linear mixed models, to take into account for multiple measurements, will be performed.

Confounding factors will also be taken into account in the analyses in the case of unbalanced distribution between groups.

### Subgroup analyses

It is possible that some patients will already have high dietary intake of omega-3. Subgroups analyses will be carried out to explore how baseline levels of omega-3 in the diet can modify the effect of the intervention. The effect of the intervention will be tested for low or high levels of total omega-3 (and LCn3) using intake with an interaction term in the multivariable linear regression. The levels measured in red blood cells, a good proxy to the diet, will also be evaluated. The cutoff will be the recommended dietary intake of 1.6 g daily [73] for total omega-3 and 250 mg for EPA (the equivalent of approximately 8 oz per week of a variety of seafood [74]). For red blood cells levels, the value corresponding to the recommended dietary intake (modeled in this cohort) will be used as a cutoff.

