### Omega-3 fatty acids

Long-chain omega-3 polyunsaturated fatty acids (LCn3), eicosapentaenoic acid (EPA) and docosahexanenoic acid (DHA), mainly found in seafood and fatty fish, might help lower PCa incidence and/or delay its progression [4–8]. However, some reviews reported no association [9–12] or mixed associations depending on LCn3 subtypes [13, 14]. It is important to note that observational studies are often limited by multiple sources of bias and the difficulty of estimating LCn3 intakes. LCn3 levels measured in red blood cells reflect the diet over the last 3 months [15]. However, studies that evaluated dietary LCn3 from biomarkers, assessed LCn3 in the plasma [9–11, 16–18], a measure that reflects the diet of the past few days [15]. Interestingly, we have recently measured LCn3 in the targeted prostate tissue during active surveillance of patients with a low-grade PCa. We observed a significant protective association between higher levels of EPA and a lower risk of progression to high-grade PCa [19].

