### Sample size calculation

Sample size analysis was done using a two-sample t-test for a log-normal geometric mean ratio with a two-sided significance level of 0.05, assuming equal variances. Based on published data [28, 29], we assume a coefficient of variation of 0.4. In the study conducted by Aronson et al. [28], a statistically significant reduction of 32% in the proportion of cells expressing Ki-67 was observed in a group receiving a low-fat diet supplemented with fish oil compared to a control group assigned to a Western diet. We determined that, for the primary outcome, a total of 126 patients (63/group) will provide 90% power [69, 70] to detect a mean ratio of the proportions of cancer cells expressing Ki-67 of ≤0.8, i.e. a 20% difference across groups. We estimate ≤3% drop out before RP (occurring in ≤1% at our institution). Based on these estimation, the sample size needed for the trial will be 130 patients (65/group).

Twelve months after RP, we expect a 5 to 10% loss to follow-up, which will affect only secondary outcomes. In absence of published data on the effects of omega-3 supplementation on inflammation mediators, we used Cohen’s *d* to calculate effect sizes [71]. A total sample size of 116 will provide 80% statistical power to detect a moderate or large effect size (≥0.5). This sample size will also be sufficient to detect expected between-groups differences on quality of life dimensions. Indeed, LCn3 supplementation reduced anxiety by 20% (d = 0.51) in one study [51] and it yielded a moderate effect size (d = 0.61) for treating depressive disorders (vs. placebo) in another [72]. For these effect sizes in our final sample, we evaluate a power of 80% to detect an effect for anxiety and a power of 92% to detect an effect for depressive symptoms.

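### The omega-3 effect-modification analysis names LCn3 but sets its second cut-off for EPA alone, leaves the red-cell cut-off to be modelled from trial data, and tests only a low/high split

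*Protocol article*

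**What the plan says.** The Subgroup analyses section of the Protocol article sets out to explore whether men who already eat a lot of omega-3 respond differently. The modifier is introduced as follows: "The effect of the intervention will be tested for low or high levels of total omega-3 (and LCn3". The test is an interaction term in the multivariable linear regression.

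The intake cut-offs come two sentences later: "The cutoff will be the recommended dietary intake of 1.6 g daily [73] for total omega-3 and 250 mg for EPA". The 250 mg value is explained as roughly what 8 oz of varied seafood per week supplies. For red blood cells, "the value corresponding to the recommended dietary intake (modeled in this cohort) will be used as a cutoff".

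Two other places fix the vocabulary. The Background section on omega-3 fatty acids defines the term, "Long-chain omega-3 polyunsaturated fatty acids (LCn3), eicosapentaenoic acid (EPA) and docosahexanenoic acid (DHA", and says that these acids come mainly from seafood and fatty fish. The Rationale calls EPA a sub-type of LCn3.

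The article gives no baseline distribution of intake or red-cell levels, no expected share of men above any cut-off, and no power for the interaction. Its statement that two-sided p-values below 0.05 count as significant covers all analyses.

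**The concern.** Three features of this short section make its result harder to interpret than it need be.

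- **Variable and cut-off.** The second modifier is LCn3, but the second cut-off is for EPA. On the article's own definition these are different quantities, so an analyst cannot classify a man as low or high on LCn3 from the text.
- **Red-cell cut-off.** No number is fixed. The value is to be estimated from the relation between red-cell level and questionnaire intake in about 130 men, and the text does not say whether the 1.6 g or the 250 mg intake is the reference.
- **Low/high split.** A continuous modifier is reduced to two groups, in a trial sized for the main effect and therefore already weak for an interaction.

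At stake is whether the exploratory result can be reproduced, and how much of the available information it uses. The primary Ki-67 comparison does not depend on it.

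**Working it through.** **1. Variables against cut-offs**

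| Modifier named | Cut-off given | Match |
|---|---|---|
| Total omega-3 intake | 1.6 g daily | Yes |
| LCn3 intake (EPA and DHA) | None | No |
| (EPA intake, not named as a modifier) | 250 mg | Cut-off without a named modifier |
| Red-cell level | To be modelled from a recommended intake | Reference intake not named |

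The mismatch is confined to the LCn3/EPA pair.

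**2. The plan's own sample size, to confirm the inputs**

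Inputs from Sample size calculation: "two-sample t-test for a log-normal geometric mean ratio with a two-sided significance level of 0.05, assuming equal variances"; "we assume a coefficient of variation of 0.4"; "a total of 126 patients (63/group) will provide 90% power"; and a "mean ratio of the proportions of cancer cells expressing Ki-67 of ≤0.8, i.e. a 20% difference across groups".

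- Log-scale SD = √ln(1 + 0.4²) = √ln 1.16 = 0.3853.
- Effect = |ln 0.8| = 0.2231.
- n per arm = 2(1.960 + 1.282)² × 0.3853² / 0.2231² ≈ 62.6, so 63. The normal approximation gives 90.2% power at 63 per arm. The noncentral t gives 89.7% and would ask for 64.
- Dropout: 126 / 0.97 = 129.9, so 130.

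The stated figures reproduce.

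**3. Power of the planned low/high interaction**

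Let q be the share of men in the smaller group, with 126 men and equal arms within each group. Then SE = 0.3853 × √[4/(126q) + 4/(126(1−q))]. Suppose the interaction is as large as the whole planned main effect (ratio 0.8). At q = 0.5, SE = 0.1373 and power = Φ(0.2231/0.1373 − 1.960) = 37%. The same formula gives 32% at 30/70, 26% at 20/80 and 16% at 10/90. The values of q are assumed, because the article gives none.

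**4. Information kept after splitting**

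With an interaction linear in the modifier X, the share of information kept by splitting at c is the squared correlation of X with the indicator X > c. For a normal X this is E = φ(z_q)² / [q(1−q)]. The equivalent sample is 126 × E. A continuous test with 80% power falls to Φ[(1.960 + 0.842)√E − 1.960].

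| Split | Kept (E) | Lost | Equivalent of 126 men | 80% power becomes |
|---|---|---|---|---|
| 50/50 | 0.637 | 36.3% | 80.2 | 61% |
| 30/70 | 0.576 | 42.4% | 72.5 | 57% |
| 20/80 | 0.490 | 51.0% | 61.7 | 50% |
| 10/90 | 0.342 | 65.8% | 43.1 | 37% |

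Other shapes, by simulation with 1,000,000 draws:

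- Uniform modifier: 25% lost at the median, 28% at 40/60, 37% at 30/70.
- Log-normal modifier (log-SD 0.3 to 1.0), interaction linear in untransformed X: 37% to 95% lost over the cut points tried.
- True step exactly at the cut-off: nothing is lost by splitting. With a normal modifier and a step at its median, a linear term would itself lose about 36%.

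**5. Red-cell cut-off**

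It is obtained by relating red-cell level to intake, so its precision depends on that relation. The article's own descriptions suggest some slack: the food questionnaire covers the past month, red cells are said to reflect about three months, and earlier supplement users may enter after a washout of at least 8 weeks. The size of the error cannot be computed from the document. Ki-67 plays no part in the derivation.

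**The case against.** The strongest reply is that this is an exploratory analysis with sensible features. It uses a formal interaction term rather than separate subgroup p-values, and its intake cut-offs are external values set in advance. Asking whether men above a recommended intake respond differently is a legitimate question, and a split at that intake answers it directly. If the effect really changes at that level, the split is the better test. The questionnaire's omega-3 assessment was validated in prostate cancer patients. How the red-cell value is modelled is detail that a SAP may hold. An EPA cut-off could also be deliberate, since the intervention is EPA.

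Most of this stands and limits the point. It does not remove the mismatch: if EPA was intended, the modifier should be called EPA. It also does not settle which intake the red-cell value corresponds to.

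Several stronger readings are tempting but unsupported:

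- A reader might infer that both intake cut-offs are misaligned. The 1.6 g one is not.
- A reader might infer two competing 250 mg rules. No sentence sets 250 mg for LCn3; the defect is a missing cut-off. Whether EPA is a slip for EPA plus DHA depends on a cited source that is not at hand.
- A reader might take the modelled red-cell value for an outcome-driven cut-off. It is derived from intake, so it does not by itself inflate type I error.
- A reader might expect very few men in the high group. The article has no intake data to show this.

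**Conclusion.** The point holds as a modest one. LCn3 is named as a modifier but has no matching cut-off. The red-cell cut-off is not fixed as a number, carries estimation error, and is not tied by name to either intake value.

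The information cost of splitting is real under common assumptions but is not a fact of this trial. It is about 36% to 66% for a normal modifier with a linear interaction (50/50 to 90/10 split), about 25% for a uniform modifier at its median, and zero for a true step at the cut-off. It would be wrong to say without those conditions that at least a third of the information is discarded. The low power of the split test (37% at best over the splits tried, for an interaction as large as the planned main effect) rests on the plan's own SD and on assumed group shares.

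The primary result is not affected. This is a cheap improvement, not a defect that threatens the trial's conclusion.

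**What to change.** 1. Make the modifier and the 250 mg cut-off name the same quantity, either EPA or EPA plus DHA, and use it throughout the section.
2. Make arm by continuous baseline value the main interaction test, using log-transformed intake and the red-cell level at V0. Show the estimated treatment effect with its 95% CI at a few values, including the recommended intake.
3. Keep the low/high split as description only.
4. If a red-cell cut-off is kept, fix its derivation rule, and the intake it corresponds to, before unblinding.

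The cost is a change of wording in the protocol or SAP. Table 1 already schedules the food questionnaire and blood sample at V0, so no new collection is needed. The downside is that the continuous test assumes a roughly linear interaction and is less efficient if there is a true threshold; the retained low/high description would help to show one.

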### Ethical considerations

The study protocol has been approved by the ethics committee of CHU de Québec - Université Laval (2012–1012). Written informed consent is obtained from all randomized patients for the study as well as for biobanking of their biological specimens (blood, urine, tissue).

### Adverse events safety monitoring

Many studies have already shown LCn3 safety. Therefore, no major harmful effects are expected. However, adverse events will be monitored at each visit post-prostatectomy using the NIH criteria for adverse events (v4.03, June 2010). An independent safety monitoring board includes a statistician [name] (PhD), Head of Applied Clinical Research Unit of CHU Sainte-Justine Research Center, Montréal, Quebec and a prostate cancer and clinical research trial expert, [name] (MD), Centre Hospitalier de l’Université de Montréal Research Center, Montreal, Quebec.

### Data collection, managing and monitoring

All data is collected at the research center by research professionals. Questionnaires are scanned and validated by a research professional. The data is stored on the network of the Centre de recherche du CHU de Québec – Université Laval following their Standard Operative Procedures to ensure confidentiality. Only the PI and the research professionals implied in the current study will have access to the data and protected by a password. Questionnaires will be stored in a locked filing cabinet which is in a locked room. Data collection follow-up monitoring will be realized on a regular basis by the research team.

## Discussion

This trial is the first to examine the effects of preoperative LCn3 supplementation with Ki-67 as a primary outcome. Moreover, it is, to our knowledge, the first to examine the effects of LCn3 on inflammation and quality of life among PCa patients. Well conducted RCTs assessing the effect of LCn3 on PCa outcomes are important as conflicting results from observational studies do not allow conclusions to be drawn so far. In fact, the need for prospective RCTs to identify specific nutrients for PCa patients has recently been highlighted [4]. This trial will contribute to the improvement of available evidence for clinicians and PCa patients who want reliable information on lifestyle strategies to improve survivorship and quality of life [75]. PCa patients would benefit from interventions harbouring few or no side effects. As such, lifestyle and nutritional interventions are appealing as they are innocuous and have the potential to improve various clinically relevant outcomes. High quality trials are important to allow these interventions to be offered to patients in combination with other established treatments.

## Status of the trial

The first patient was enrolled on February 12, 2015. The enrollment and randomization of the planned 130 patients was completed on June 9, 2017. The data collection is expected to end in August 2018.

## Abbreviations

EPIC-26: Expanded Prostate Index Composite score
FACT-COG: Functional Assessment of Cancer Therapy – Cognitive Function
FCRI: Fear of Cancer Recurrence Inventory
FFQ: Food frequency questionnaire
FSI: Fatigue symptoms inventory
HADS: Hospital Anxiety and Depression Scale
HOSO: high oleic acid sunflower oil
IPSS: International Prostate Symptoms Score
LCn3: long-chain omega-3 polyunsaturated fatty acids
LOS: Limit of sensitivity
MAG-EPA: eicosapentaenoic acid monoacylglyceride
OCT: Optimal cutting temperature
PCa: Prostate cancer
RCT: Randomized controlled trial
RP: Radical prostatectomy
SOP: Standard operating procedures
